#### Opposing needling plus electroacupuncture (OE)

2.6.1

Acupuncture will be administered bilaterally, including both the side with more significant pain and the contralateral side, which presents with mild or no pain. The selected acupoints include, Zusanli (ST36, bilateral), Yanglingquan (GB34, bilateral), Xuehai (SP10, bilateral), Liangqiu (ST34, bilateral), Dubi (ST35, more affected side), Neixiyian (EX-LE4, more affected side), Yinlingquan (SP9, more affected side), and Ashi points (more affected side). Acupoint locations will be determined according to the National Standard of the People’s Republic of China, *Nomenclature and Location of Acupuncture Points* (GB/T 12346–2021). Figure 2 illustrates the anatomical locations of these acupoints.

**Figure 2 fig2:**
[figure not shown]
Acupuncture point diagram. Screenshot from the mobile application ‘Zhiyuan Meridian and Acupoint’ (知源经络穴位) (https://apps.apple.com/app/id1554030035), with local knee acupoints labeled by the authors. Copyright permission for academic use has been obtained.

This trial will use Chinese HWATO stainless steel filiform needles (0.30 mm × 25 mm and 0.30 mm × 40 mm) and the Chinese HWATO SDZ-III Low-Frequency (1–100 Hz) Pulse Electronic Acupuncture Stimulator Machine, with 6 channels, and adjustable output power (0.3–10 V at 250 ohms).

Prior to the procedure, the acupuncturists will wash their hands with antiseptic hand sanitizer and disinfect the skin at each acupoint site using a 75% alcohol swab in a circular motion from the center outward. Needle insertion depth will be determined based on the specific anatomical characteristics of each acupoint. The twisting technique will be used to elicit Deqi sensation, characterized by soreness, numbness, heaviness, distension, warmth, coolness, or the transmission of needling sensation, while the acupuncturists perceive resistance or tension beneath the needle.

Once Deqi sensation is achieved, a twirling-rotating method with even manipulation will be applied using a twisting angle of approximately 180° at a frequency of 120–160 times per minute. Electroacupuncture will be applied to the more affected knee for 30 min. Two pairs of output wires will be connected: one pair from Liangqiu (ST34, anode) to Yanglingquan (GB34, cathode) on the lateral side, and another from Yinlingquan (SP9, anode) to Xuehai (SP10, cathode) on the medial side. A dense-disperse wave of 2/100 Hz will be selected, and the electrical current will be gradually increased until the patient experiences a mild, rhythmic muscle twitching around the acupoints without discomfort.

After 30 min of stimulation, the acupuncturists will press a dry cotton ball around the needle site with one hand and simultaneously rotate and withdraw the needle slowly with the other hand. Gentle pressure will be applied to the insertion site to prevent bleeding.

#### Sham opposing needling plus electroacupuncture (SE)

2.6.2

Both knees received acupuncture treatments. The acupuncture protocol on the more affected side was identical to that used in the OE group, while four non-acupoint, non-meridian sites on the contralateral calf—distant from the knee and with mild or no pain—were selected for sham opposing needling. The anatomical locations of these sites are illustrated in Figure 3 and detailed in Supplementary File 1 and Table 2.

**Figure 3 fig3:**
[figure not shown]
Diagram of non-meridian and non-acupoint locations for the SE group. Screenshot from the mobile application ‘Zhiyuan Meridian and Acupoint’ (知源经络穴位) (https://apps.apple.com/app/id1554030035), with local knee acupoints labeled by the authors. Copyright permission for academic use has been obtained.

**Table 2 tab2:** Detailed description of non- meridian and non-acupoint locations.

Non-meridian and non-acupoint	Acupoint localization
1	6 cun superior to the patella, approximately 1 cun (roughly 2 cm) between the Spleen and Stomach meridians
2	4 cun superior to the patella, between the Spleen and Stomach meridians
3	2 cun posterior to Fengshi (GB31), avoiding the Bladder meridian
4	1 cun medial to Chengjin (BL56)

Sham opposing needling will be performed using the Park sham device (35), which features a blunt, retractable needle tip designed to mimic the sensation of skin penetration without actual insertion. Each needle is supported by a circular adhesive base affixed to the skin surface. The structural principle of the Park sham device is illustrated in Figure 4.

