### Blinding

2.5

Participants, outcome assessors, and statisticians will be blinded to group allocation throughout the study. To maintain blinding, the three groups will be referred to as the OE group, SE group, and EA group, respectively. Due to the particularity of acupuncture, acupuncturists will not be blinded. Acupuncture treatments, outcome assessments, and statistical analyses will be conducted independently by different members of the research team.

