**Figure 4 fig4:**
[figure not shown]
Structural principle of the Park sham device.

All four non-acupoint sites will undergo perpendicular sham opposing needling. Because of the blunt needle tip, the skin will not be penetrated, and the needles will be supported by the circular bases. To minimize bias from psychological effects, a standardized twirling–rotating manipulation, including amplitude and frequency, will be performed to match the procedure used in the OE group.

After the 30-min intervention, the sham device will be removed. The acupuncturists will press a dry cotton ball over each site while simulating needle withdrawal using the same technique as in the OE group to ensure consistency in the treatment procedure.

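### Sections 2.6.1 and 2.6.2 describe an adhesive base only under the contralateral sham needles, which may weaken participant blinding between OE and SE

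*Protocol article*

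**What the plan says.** Section 2.5 makes the blinding claim without reservation: "Participants, outcome assessors, and statisticians will be blinded to group allocation throughout the study". Only the acupuncturists are excepted.

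Section 2.6.1 describes OE: "This trial will use Chinese HWATO stainless steel filiform needles". It goes through disinfection, insertion, manipulation and electrical stimulation. At the end the acupuncturist is to "press a dry cotton ball around the needle site with one hand and simultaneously rotate and withdraw the needle slowly with the other hand". No base, ring or guide is mentioned, and no device is taken off the skin.

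Section 2.6.2 describes SE. For the more affected side: "The acupuncture protocol on the more affected side was identical to that used in the OE group". For the contralateral side: "Sham opposing needling will be performed using the Park sham device". Of that device it says: "Each needle is supported by a circular adhesive base affixed to the skin surface". It later repeats, for the four sham sites, that "the needles will be supported by the circular bases", and ties this to the blunt tip not entering the skin. A device-removal step after the session appears here only. The twirling, with its amplitude and frequency, is standardized "to match the procedure used in the OE group", and the simulated withdrawal also follows the OE technique.

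The Discussion supports OE/SE blinding by noting that both arms are needled on both sides.

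**The concern.** A non-penetrating needle protects blinding best when the real needle is presented in the same way. If the base sits only under sham needles, it is a feature that SE participants can see, and perhaps feel, and that OE participants never meet. It recurs at each of the 24 sessions. It is also a within-person contrast: an SE participant can compare one leg with the other and does not need to see another arm.

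This matters most for OE versus SE. The EA arm is needled on one side only, so the sham comparison carries the argument that opposing needling works beyond expectation. The primary outcome (WOMAC) and the pain, function and quality-of-life scales rest mainly on what participants report, and blinded assessors do not remove expectation from such reports. The eligibility criteria exclude acupuncture only within the past 3 months, so people who know ordinary needling can enrol. If some SE participants came to suspect the sham, the likely direction of bias would favour OE.

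**Working it through.** No sample-size or error-rate formula applies, and the plan gives no figure to reproduce. The check sets the arm descriptions in Sections 2.6.1 to 2.6.3 side by side.

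| | OE | SE | EA |
|---|---|---|---|
| More affected side | Filiform needles, electroacupuncture; no base described | Same as OE | Same as OE |
| Contralateral side: needle | Filiform needles at ST36, GB34, SP10, ST34 | Park sham needles at four non-acupoint sites | None |
| Contralateral side: base | None described | Adhesive base under each needle | Not applicable |
| End of session, contralateral | Cotton ball, needle withdrawn | Sham device removed, withdrawal simulated with cotton ball | Not applicable |

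1. The number of contralateral needles agrees: the four bilateral points in OE against four sham sites in SE. Needle count is therefore not a cue.
2. The features that 2.6.2 expressly matches to OE are the twirling manipulation (amplitude and frequency) and the withdrawal technique. The base and the look of the needle are not on that list.
3. The reason given for the base is the blunt tip, which applies only to the sham. Nothing in 2.6.1 gives a reason to use a base with a penetrating needle, and none is mentioned.
4. Reading across the rows, an SE participant meets two set-ups in each session (with a base on one leg, without on the other). An OE participant meets one.
5. The Discussion's argument, bilateral needling in both arms, deals with which legs are needled. It does not deal with how the needles look.

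On size, the planning means in Section 2.3 give SE minus EA as 22.42 − 8.87 = 13.55 WOMAC points and OE minus SE as 32.3 − 22.42 = 9.88 points, both in favour of the first-named arm. Turning either into a bias would need the share of participants who notice the base, the share who take it for a sham, and the effect of that belief on WOMAC. The documents give none of these.

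**The case against.** The strongest objection is that the point rests on silence. No sentence says that real needles are placed without a base, and the sentence about the base describes how the Park device is built. The article is condensed. Section 2.6 refers to a standard operating procedure that covers use of the Park needles, and Figure 4 is not available here, so bases under all needles may be specified elsewhere. This stands as a limit on the claim: the documents do not show that OE needles are bare. It does not remove the point. The article mentions the base twice, both times for the sham, gives the OE procedure in detail without it, and omits it from the matched features.

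Second, a reader might infer that SE participants will be unblinded. The documents do not support that. Participants do not see other arms, and nothing says they are told that a base marks a sham. The two legs also differ in OE, where only the more affected side carries electrode wires and the additional points, so some asymmetry is expected under real treatment too. What remains is one further cue, present in SE and absent in OE.

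Third, a reader might treat the 13.55-point SE-minus-EA step as a non-specific effect and take a percentage of it as the inflation of OE minus SE. Any such percentage would be invented, and Section 2.3 offers these means only as planning assumptions.

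Fourth, identical bases would not equalize site location, skin penetration or Deqi. That is true. It limits what the change can achieve, but the cue can still be removed.

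**Conclusion.** The point holds in limited form. As described, the adhesive base and its removal belong only to the contralateral sham in SE, and the base is not among the features matched to OE. Followed as written, OE and SE differ in a visible feature on the contralateral leg, and this may weaken the participant blinding claimed in Section 2.5 for that contrast. Any resulting bias would probably favour OE, but its size cannot be computed from the documents.

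This rests on two assumptions: that the full procedure does not already place real needles through bases, and that participants can see or feel the base. If bases are already used under the OE contralateral needles, only the text needs correcting. Neither proven unblinding nor a bias in WOMAC points can be concluded.

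**What to change.** State in Section 2.6.1 that the OE contralateral needles are placed through the same adhesive base as the Park sham and taken off with the same removal step, and add the base to the features listed in 2.6.2 as matched. Leave the more affected side as it is, the same in all three arms; bases there are not needed for the OE/SE match and would have to be reconciled with the electrode wiring. If the base is not used in OE, qualify the participant-blinding statement in Section 2.5 to say that OE and SE needles differ in appearance on the contralateral side.

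The cost is small: four contralateral points × 24 sessions = 96 bases per OE participant, or 96 × 36 = 3,456 for a full OE arm, plus slightly more preparation time and a line in the operating procedure. Before adoption, check that the base allows the intended insertion of the real needle. The differences in site location, penetration and Deqi would remain.

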**Figure 4 fig4:**
[figure not shown]
Structural principle of the Park sham device.

All four non-acupoint sites will undergo perpendicular sham opposing needling. Because of the blunt needle tip, the skin will not be penetrated, and the needles will be supported by the circular bases. To minimize bias from psychological effects, a standardized twirling–rotating manipulation, including amplitude and frequency, will be performed to match the procedure used in the OE group.

After the 30-min intervention, the sham device will be removed. The acupuncturists will press a dry cotton ball over each site while simulating needle withdrawal using the same technique as in the OE group to ensure consistency in the treatment procedure.

#### Electroacupuncture alone

2.6.3

The more affected side will receive acupuncture treatment following the same needling procedures, acupoint selection, and electroacupuncture protocol as the more affected side in the OE group.

#### Rescue therapy

2.6.4

During the treatment period, if the participant experiences a significant exacerbation of pain that becomes intolerable, a rescue dose of celecoxib (200 mg) will be permitted. The acupuncturists will record the use of any rescue therapy in detail. Aside from this provision, the use of any additional analgesics is strictly prohibited throughout the study period. Participants will also be prohibited from receiving any other treatments related to KOA, including joint injections of any kind, moxibustion, cupping, tuina massage, or similar interventions.

#### Basic treatment

2.6.5

All enrolled participants will receive basic health education, with the content based on the Consensus of Four-Stepladder Program of Knee Osteoarthritis (2019) issued by the Chinese Orthopedic Association.The specific educational components are as follows:(1) Providing patients with information about KOA to enhance their understanding of the disease;(2) Instructing patients on weight management through dietary modifications and functional exercise, advising them to avoid unnecessary weight-bearing activities (e.g., carrying heavy objects, climbing stair), refraining from excessive physical exertion to prevent joint injury, and maintaining warmth to protect the joints;(3) Encouraging patients to engage in appropriate muscle-strengthening exercises for the joints, such as aerobic activities, Tai Chi, and Baduanjin.

#### Treatment schedule

2.6.6

Each treatment session will last for 30 min. Participants will receive treatments three times per week, over a period of 8 consecutive weeks, for a total of 24 sessions.

#### Baseline information

2.6.7

On day 0 of the trial, general clinical data will be collected for all participants, including disease duration (months), affected knee(s), radiographic grading (X-ray), prior treatments (medications, pharmacologic therapy, electroacupuncture or opposing needling, etc.), and concomitant systemic diseases. These baseline data will be used to describe participant characteristics and to account for potential confounding factors in the statistical analysis, providing a reference for the assessment of primary, secondary, and other observational outcomes.

### Outcome measurements

2.7

All outcome measures will be assessed at baseline, at the end of the 4th week, and at the end of the 8th week. Additionally, WOMAC, NRS, and SF-36 will be reassessed at the end of the 12th week to evaluate changes in intervention effects across the OE, CE, and EA groups.

#### Primary outcome

2.7.1

##### The Chinese version of the Western Ontario and McMaster universities osteoarthritis index (WOMAC) score for the more affected knee

2.7.1.1

During the trial, the WOMAC score of the more affected knee will be assessed at baseline and at weeks 4, 8, and 12. The primary analysis will focus on the change from baseline to week 8 to evaluate the treatment effect, while scores at other time points will be used to assess the trend and maintenance of efficacy.

#### Secondary outcomes

2.7.2

##### WOMAC pain subscale score

2.7.2.1

During the trial, the WOMAC pain subscale score of the more affected knee will be assessed at baseline and at weeks 4, 8, and 12. The primary analysis will focus on the change from baseline to week 8 to evaluate the treatment effect, while scores at other time points will be used to assess the trend and maintenance of efficacy.

##### WOMAC stiffness subscale score

2.7.2.2

During the trial, the WOMAC stiffness subscale score of the more affected knee will be assessed at baseline and at weeks 4, 8, and 12. The primary analysis will focus on the change from baseline to week 8 to evaluate the treatment effect, while scores at other time points will be used to assess the trend and maintenance of efficacy.

##### WOMAC function subscale score

2.7.2.3

During the trial, the WOMAC physical function subscale score of the more affected knee will be assessed at baseline and at weeks 4, 8, and 12. The primary analysis will focus on the change from baseline to week 8 to evaluate the treatment effect, while scores at other time points will be used to assess the trend and maintenance of efficacy.

##### Visual analog scale

2.7.2.4

During the trial, the VAS score of the more affected knee will be assessed at baseline and at weeks 4, 8, and 12. The primary analysis will focus on the change from baseline to week 8 to evaluate the treatment effect, while scores at other time points will be used to assess the trend and maintenance of efficacy.

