### Trial design

2.1

This is a three-armed RCT conducted at the Rehabilitation Department of the Thirteenth People’s Hospital of Chongqing and the Rehabilitation Department of Chengdu Pidu District Traditional Chinese Medicine Hospital. The total duration of the trial will be 12 weeks, comprising an 8-week intervention period followed by a 4-week follow-up period. A flow chart of the clinical trial procedure is presented in Figure 1, and the schedule of outcome measurements is detailed in Supplementary File 1 and Table 1.

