##### Global pain scale

2.7.2.6

During the trial, the GPS score of the more affected knee will be assessed at baseline and at weeks 4, 8, and 12. The primary analysis will focus on the change from baseline to week 8 to evaluate the treatment effect, while scores at other time points will be used to assess the trend and maintenance of efficacy.

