##### Lequesne functional index (Lequesne index)

2.7.2.7

During the trial, the Lequesne index score of the more affected knee will be assessed at baseline and at weeks 4, 8, and 12. The primary analysis will focus on the change from baseline to week 8 to evaluate the treatment effect, while scores at other time points will be used to assess the trend and maintenance of efficacy.

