##### Knee injury and osteoarthritis outcome score

2.7.2.8

During the trial, the KOOS of the more affected knee will be assessed at baseline and at weeks 4, 8, and 12. The primary analysis will focus on the change from baseline to week 8 to evaluate the treatment effect, while scores at other time points will be used to assess the trend and maintenance of efficacy.

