### Adverse events

2.8

All trial investigators, responsible units, clinical monitors, and participants must record and promptly report any AEs to the project leader and study team, regardless of their relationship to the study intervention. AEs should be documented in the source documents and case report forms (CRFs), including a description of the event, onset time, duration, severity, frequency, interventions administered, outcome, and the investigator’s assessment of causality. Common AEs associated with acupuncture and electroacupuncture include fainting, needle retention, needle breakage, local pain, bleeding, or subcutaneous bruising, which are generally mild to moderate. Investigators should provide appropriate symptomatic management according to the participant’s condition and continue follow-up until the participant’s condition stabilizes. Relevant clinical data should be properly preserved to support AE evaluation and reporting.

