### Statistical analysis

2.12

Demographic Data Analysis: To assess the comparability between the three groups, demographic data and other baseline characteristics were compared. Continuous variables, such as age and Body Mass Index (BMI), were analyzed using independent-samples *t*-tests, provided that the data met the normality assumption. If the data did not meet the normality assumption, non-parametric tests, such as the Kruskal-Wallis test, were used. Categorical variables, such as gender, were analyzed using χ^2^ tests, ensuring that the assumptions for the test (e.g., adequate sample size in each category) were satisfied.

Clinical Efficacy Analysis: A multivariate analysis of covariance (ANCOVA) was performed to assess efficacy outcomes, with age, BMI, and disease duration included as covariates. The primary and secondary outcome measures were clearly defined, and potential confounding factors were controlled to ensure the robustness of the results.

Safety Analysis: The incidence of AEs and SAEs at 8 weeks post-randomization was compared across the three groups using χ^2^ tests. All AEs and SAEs were documented and analyzed to assess the safety of the interventions in each group.

Handling of Missing Data: After data collection is completed, the proportion, distribution, and possible mechanisms of missing data [e.g., missing completely at random (MCAR) or missing at random (MAR)] will be examined. For outcomes with a low proportion of missing data (≤5%) (36) and no apparent systematic pattern, complete-case analysis will be performed. If the proportion of missing data is higher or systematic missingness is observed, multiple imputation will be applied under the assumption of missing at random to reduce bias and maximize data utilization. Sensitivity analyses will be conducted to assess the robustness of the results under different missing data handling approaches. All analyses will be performed using R software (R version 4.4.3).

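### Week-12 assessment of VAS, GPS, Lequesne and KOOS is scheduled in four outcome sections but not in section 2.7 or Table 1; the between-group AE comparison covers only 8 of the 12 weeks

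*Protocol article*

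**What the plan says.** **Efficacy schedule.** Section 2.7 has all outcomes measured at baseline, week 4 and week 8, and then names the instruments that are repeated after treatment: "Additionally, WOMAC, NRS, and SF-36 will be reassessed at the end of the 12th week". Table 1 agrees. WOMAC, NRS and SF-36 carry four marks each; VAS, GPS, Lequesne and KOOS carry three, with the follow-up column empty.

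The individual outcome sections say otherwise for those four instruments:

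- Section 2.7.2.4: "the VAS score of the more affected knee will be assessed at baseline and at weeks 4, 8, and 12".
- Section 2.7.2.6: "the GPS score of the more affected knee will be assessed at baseline and at weeks 4, 8, and 12".
- Section 2.7.2.7: "the Lequesne index score of the more affected knee will be assessed at baseline and at weeks 4, 8, and 12".
- Section 2.7.2.8: "the KOOS of the more affected knee will be assessed at baseline and at weeks 4, 8, and 12".

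Each of these sections puts its main analysis at week 8 and uses the other visits to describe the course of the effect and whether it lasts.

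**Safety.** Section 2.1 states: "The total duration of the trial will be 12 weeks, comprising an 8-week intervention period followed by a 4-week follow-up period". Under section 2.8 investigators, monitors and participants "must record and promptly report any AEs to the project leader and study team", with no end date. Table 1 marks AE assessment once, at week 8. Section 2.12 states: "The incidence of AEs and SAEs at 8 weeks post-randomization was compared across the three groups". Its next sentence adds that every AE and SAE is documented and analysed.

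**The concern.** The two efficacy schedules cannot both be followed. For four secondary outcomes the article promises week-12 results in one place and excludes them in another. Two things follow.

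First, a later report could include or leave out week-12 results for these scales and be consistent with the published protocol either way. A reader could not tell a planned omission from a selective one.

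Second, the missing-data rule in section 2.12 depends on which assessments were planned. It uses complete cases when at most 5% of an outcome is missing without a systematic pattern, and multiple imputation otherwise. If week 12 is scheduled for KOOS, an absent score counts towards that proportion. If it is not scheduled, there is nothing to count.

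The safety point is of a different kind. The text does not contradict itself outright, but its parts do not fit together well. AEs must be recorded without a time limit and all are to be analysed, yet the only scheduled AE assessment and the only stated comparison between groups end with treatment. An event in weeks 9 to 12 would be recorded but has no place in that comparison.

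**Working it through.** No sample-size or power figure enters this point, so the check sets the sections side by side.

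**Step 1: week 12 by instrument.** WOMAC subscales are counted with WOMAC.

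| Instrument | Section 2.7 | Table 1 | Own outcome section | Agree? |
|---|---|---|---|---|
| WOMAC | yes | yes | yes (2.7.1.1) | yes |
| NRS | yes | yes | yes (2.7.2.5) | yes |
| SF-36 | yes | yes | yes (2.7.2.9) | yes |
| VAS | no | no | yes (2.7.2.4) | **no** |
| GPS | no | no | yes (2.7.2.6) | **no** |
| Lequesne | no | no | yes (2.7.2.7) | **no** |
| KOOS | no | no | yes (2.7.2.8) | **no** |

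Section 2.7 and Table 1 schedule 3 instruments at week 12; the outcome sections schedule 7. The difference is 7 − 3 = 4.

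**Step 2: could this be a damaged table?** No. The prose of section 2.7 names the same three instruments that Table 1 marks, so the conflict stands without the table.

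**Step 3: how many assessments are in doubt?** With 108 participants and no dropout, 4 × 108 = 432. With the 20% dropout that section 2.3 allows for, and assuming that all of it falls before week 12, 432 × 0.8 is about 346. These figures are ceilings on the number of forms in doubt. They do not measure any effect on a result.

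**Step 4: safety coverage.**

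| Item | Period covered | Source |
|---|---|---|
| Trial | 12 weeks (8 treatment + 4 follow-up) | 2.1 |
| AE recording | no end date | 2.8 |
| SAE follow-up | until the condition is stable | 2.9 |
| Scheduled AE assessment | one mark, week 8 | Table 1 |
| Between-group AE/SAE comparison | 8 weeks from randomisation | 2.12 |
| General statement on analysis of AEs | all events, no window | 2.12 |

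The part of the trial outside the comparison is (12 − 8)/12 = 33%. Table 1 has no scheduled AE assessment after week 8. It also marks trial completion at week 8, which fits poorly with a trial that lasts 12 weeks.

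**The case against.** **On the schedule.** The outcome sections repeat nearly the same sentence, so the week-12 reference may be a copied phrase and not a second operating schedule. One database is built from the CRF items (section 2.11), which suggests a common form at both centres. Supplementary File 1, which is not shown, may settle what is done in practice. Week 12 has only a supporting role in the four sections, and WOMAC, NRS and SF-36 still cover pain, function and quality of life at that visit. All of this is fair, and it limits the importance of the point. It does not remove the contradiction, because nothing in the article says which text governs.

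A reader might infer that the two centres will collect different data. The documents do not support that: nothing indicates that each centre follows a different section, and the common database points the other way.

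**On safety.** A reader might infer that safety assessment stops at week 8, or that a third of the trial lies outside any AE analysis. Neither is supported. Section 2.8 sets no end date for recording, section 2.9 follows SAEs until the condition is stable, and section 2.12 says that all events are analysed. Only the scheduled mark and the between-group comparison end at week 8. An 8-week window can also be defended, because envelopes are opened immediately before the first treatment, treatment lasts 8 weeks, and the AEs listed as common in section 2.8 are largely procedural. What stands is that the article gives no reason for the shorter window and does not connect it with its general statement about all events.

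**Conclusion.** The schedule contradiction holds and is exact: four of seven instruments (VAS, GPS, Lequesne, KOOS), at one visit. Its consequence is ambiguity about what was planned, which leaves room for selective reporting of week-12 results and makes the missing-data rule uncertain there. This rests on the article's text alone; the documents do not show which schedule was intended.

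The safety point holds in a limited form. The scheduled AE assessment and the between-group comparison cover 8 of 12 weeks, while recording is open-ended and all events are said to be analysed. Extending the comparison is an inexpensive improvement; it does not correct a failure to monitor safety.

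The primary analysis is untouched. It uses the change in WOMAC from baseline to week 8, and the WOMAC schedule is the same in all three places.

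**What to change.** 1. Before the first week-12 visit, adopt one schedule for both centres, in one of two ways:
   - remove week 12, and the use of these scales to show lasting effect, from sections 2.7.2.4, 2.7.2.6, 2.7.2.7 and 2.7.2.8; or
   - add four week-12 marks to Table 1 and name the four instruments in section 2.7.

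   Either choice settles the matter, provided that the CRF and any supplementary schedule agree with it. The first adds no data collection. The second adds four questionnaires to a visit that already takes place. The timing matters because scores not collected at week 12 cannot be recovered reliably later.
2. Add an AE mark at the week-12 visit in Table 1, and clarify the trial-completion mark at week 8.
3. In section 2.12, report the between-group AE and SAE comparison through week 12 and keep the 8-week figure as the treatment-period result. The cost is a few AE questions at an existing visit and slightly more analysis.
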